## Abstract

**Background:**

Cisplatin is a potent chemotherapeutic agent, but its nephrotoxicity, which results in acute kidney injury (AKI), often limits its clinical application. Although many studies have attempted to target the mechanism responsible for its nephrotoxicity, no such method has been demonstrated to be effective in clinical trials. Recently, a dipeptidyl peptidase-4 (DPP4) inhibitor has been reported to have a renoprotective effect in a mouse model of cisplatin-induced AKI. Therefore, we will evaluate whether a DPP4 inhibitor protects the kidney from cisplatin-induced injury in humans.

**Methods/Design:**

This is a single-center, prospective, randomized, double-blind, placebo-controlled trial. A total of 182 participants who are scheduled for cisplatin treatment will be enrolled and randomly assigned to receive either a DPP4 inhibitor (gemigliptin) or a placebo. Participants will take the study drugs for 8 days starting 1 day before cisplatin treatment. The primary outcome of interest is the incidence of AKI at 7 days after finishing treatment with cisplatin. The secondary outcomes include changes in serum creatinine levels and estimated glomerular filtration rates from baseline to 7 days after cisplatin treatment.

**Discussion:**

This is the first clinical trial to investigate the effect of a DPP4 inhibitor on cisplatin-induced AKI.

**Trial registration:**

ClinicalTrials.gov number NCT02250872, December 26, 2014.

## Background

Cisplatin is a potent chemotherapeutic agent that is approved for the treatment of several types of cancer, including bladder cancer, cervical cancer, non-small cell lung cancer, and squamous cell carcinoma of the head and neck [1]. However, the kidneys are particularly affected by cisplatin because it accumulates there [1]. Cisplatin nephrotoxicity is manifested by hypokalemia, hypomagnesemia, and acute kidney injury (AKI), which often limit its clinical use [1–4]. Impairment of renal function is common and dose-dependent. AKI is found in 6–35 % of patients treated with a single dose of cisplatin and in 50–75 % of patients treated with multiple doses [5–7].

Abnormal renal hemodynamics and renal tubular cell toxicity resulting from oxidative stress, apoptosis, and inflammation are considered to be the mechanisms of cisplatin-induced nephrotoxicity [1, 8–14]. Different strategies targeting each mechanism of nephrotoxicity have been evaluated for their abilities to prevent and/or attenuate renal injury [1, 15, 16]. However, none of these strategies has been demonstrated to be effective in clinical trials [15].

Dipeptidyl peptidase-4 (DPP4) inhibitors are currently used in the treatment of type 2 diabetes mellitus to improve glucose tolerance by increasing the half-lives of glucagon-like peptide-1 (GLP-1) and glucose-dependent insulinotropic peptide [17, 18]. However, in addition to the glucose-lowering effects of DPP4 inhibitors, tissue-protective effects of DPP4 inhibition have been also demonstrated [19–23]. In particular, studies have shown that DPP4 inhibitors can protect the kidney from diabetic nephropathy, ischemia-reperfusion injury, and chronic kidney disease [24–28]. Recently, Kataqiri *et al*. have reported that a DPP4 inhibitor has a renoprotective effect in rodent cisplatin-induced AKI models by enhancing GLP-1 signaling [29]. Based on these reports of the effects of DPP4 inhibitors, we hypothesize that treatment with a DPP4 inhibitor will have a beneficial effect in cisplatin-induced AKI.

Therefore, we will conduct this clinical trial in patients treated with cisplatin.

## Methods/design

### Hypothesis

Treatment with a DPP4 inhibitor will prevent and/or ameliorate cisplatin-induced AKI in humans. Compared with placebo-treated patients, the incidence of AKI will be lower in DPP4 inhibitor-treated patients.

### Study design

This is a single-center, prospective, randomized, double-blind, placebo controlled study. This study is an investigator-initiated clinical trial. The study algorithm is described in Fig. 1. After enrollment, clinical follow-up will be performed 7 days after cisplatin treatment.

**Fig. 1 Fig1:**
[figure not shown]
Study algorithm

### Study participants and measurements

Cancer patients aged 18–70 years treated with intravenous cisplatin will be screened. The following will be conducted at the initial visit: (1) a questionnaire regarding active cancer history, chemotherapy, medical history, and history of nephrotoxic use including the use of nonsteroidal anti-inflammatory drugs (NSAIDs), antibiotics, contrast media, and calcineurin inhibitors; (2) a physical examination of all systems; (3) height and weight measurements; (4) blood pressure and pulse rate measurements. Participants who meet all of the inclusion and exclusion criteria and provide written, informed consent are eligible for this study (Table 1).

**Table 1 Tab1:** Inclusion and exclusion criteria

Inclusion criteria	Exclusion criteria
Age between 18 and 70	Diabetes mellitus
	Chronic kidney disease stage IV-V (eGFR <30 ml/min/1.73m^2^)
	History of transplantation
	History of acute kidney injury before randomization
	Active infection
Cancer patients treated with intravenous cisplatin	Use of other nephrotoxic agents such as nonsteroidal anti-inflammatory drugs, aminoglycosides, colistin, vancomycin, cyclosporine, tacrolimus
	Receiving contrast media during last 72 h
	Liver disease (bilirubin >2 mg/dl, transaminase levels >2.5 times the upper limit normal)
Written consent	Patients with high risks of dehydration owing to poor oral intake
	High blood pressure (>180/110 mmHg despite antihypertensive medications)
	Hypersensitivity to gemigliptin or its excipients
	Low compliance to gemigliptin treatment

Abbreviation: *eGFR* estimated glomerular filtration rate

Serum creatinine (SCr) will be measured by the isotope dilution mass spectrometry-traceable method using a Toshiba TBA 200FR Analyzer (Toshiba, Tokyo, Japan). The estimated glomerular filtration rate (eGFR) will be calculated using the Chronic Kidney Disease Epidemiology Collaboration equations (CKD EPI). The CKD EPI formula, expressed as a single equation, is eGFR = 141 × min (SCr/κ, 1)^α^ × max (SCr/κ, 1)^-1.209^ × 0.993^Age^ × 1.018 [if female] × 1.159 [if black], where κ is 0.7 for females and 0.9 for males, α is −0.329 for females and −0.411 for males, min indicates the minimum of SCr/κ or 1, and max indicates the maximum of SCr/κ or 1 [30] .

### Randomization

A research coordinator will conduct the randomization and deliver the study drug. The participants and investigators will be blinded to the treatment assignment. A list of random numbers will be generated by an independent statistician. Eligible participants will be randomly assigned 1:1 to either the treatment group or the control group in accordance with the predefined randomization list with a block size of four. The randomization will be stratified on the basis of the number of times cisplatin is administered (one or more than two) and on the cisplatin dose (< or ≥50 mg/m^2^) and will utilize a randomized block design.

### Treatments

A selective DPP4 inhibitor, gemigliptin, which is clinically available, will be used in this study. The gemigliptin and placebo tablets will be provided by LG Life Sciences (Seoul, Korea). After randomization, the participants will take either a gemigliptin (treatment group) or placebo (control group) pill for 8 days starting 1 day before cisplatin treatment. The tablet shapes and packaging of the placebo pills are identical to those of the gemigliptin pills. The prescription and administration of the study drugs will be conducted in a double-blind manner. Based on a study that reported a renoprotective effect of a DPP4 inhibitor in a mouse model of cisplatin-induced AKI [29], 100 mg/day of gemigliptin will be administered to the participants in two divided doses for 8 days starting 1 day before cisplatin treatment (Fig. 2). The administration of other nephrotoxic drugs, such as NSAIDs, aminoglycosides, colistin, and vancomycin, will be prohibited during the study, and exposure to contrast media during the 72 h prior to treatment will result in exclusion from the study. Investigators or research coordinators will evaluate drug compliance by counting pills, and participants with less than 80 % compliance will be removed from the study.

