### Outcome measures

The primary outcome of interest is the incidence of AKI at 7 days after cisplatin treatment, where AKI is defined as any of the following: an increase in SCr levels of ≥0.3 mg/dl, an increase in SCr levels of 50 % compared with baseline levels, or a decrease in the eGFR by ≥25 % compared with baseline [31–33]. The secondary outcomes will include changes in SCr levels and the eGFR compared with baseline values for 7 days after cisplatin treatment.

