### Statistical analyses

Statistical analyses will be conducted on both per protocol (PP) and intention-to treat (ITT) bases. For the PP analysis, all participants who completed the study will be included to evaluate the primary and secondary outcomes. For the ITT analysis, all participants who were enrolled and randomized to one of the two groups will be included.

The baseline characteristics and laboratory data will be presented as the means and standard deviations for continuous variables and as frequencies and percentages for categorical variables. The incidence of AKI will be compared between the two groups using a *χ*^2^ test. The differences in changes in SCr levels and in the eGFR will be analyzed using Student’s *t*-test or the Mann-Whitney *U* test. A value of *P* < 0.05 will be considered statistically significant. All analyses will be performed using SPSS Statistics software V21.0 (IBM Corporation, Armonk, NY, USA).

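### Removing randomised participants with under 80% pill compliance conflicts with the stated ITT set and can cost primary outcomes and bias the comparison

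*Protocol article*

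**What the plan says.** - **Treatments.** Study drug starts after allocation: "After randomization, the participants will take either a gemigliptin (treatment group) or placebo (control group) pill for 8 days". Compliance is judged by counting pills, and participants with under 80% "compliance will be removed from the study".
- **Statistical analyses.** "Statistical analyses will be conducted on both per protocol (PP) and intention-to treat (ITT) bases". The two sets are then defined: "For the ITT analysis, all participants who were enrolled and randomized to one of the two groups will be included", and "For the PP analysis, all participants who completed the study will be included to evaluate the primary and secondary outcomes". The PP definition contains no compliance threshold.
- **Sample size calculations.** The calculation allows for 20% dropout, but the section ends by saying that all 182 participants enter the analysis.
- **Outcome measures** and **Clinical and laboratory evaluations.** "The primary outcome of interest is the incidence of AKI at 7 days after cisplatin treatment", judged from serum creatinine and eGFR. Laboratory tests are done only twice, before and after the 8 days of study drug, so the outcome rests on the second sample.
- **Table 1.** The exclusion criteria include "Low compliance to gemigliptin treatment".

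**The concern.** Compliance with study drug can be counted only once the drug has been dispensed, so the 80% rule acts after randomisation. It removes people from the study, not from one analysis set, and no section says that they are still followed or sampled. A participant who is out of the study and has no second creatinine has no observed primary outcome, whatever the ITT definition says.

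That matters because non-compliance in the week after cisplatin need not be a chance event. Taking drug on 6 of 8 days is 75%, so two missed days are enough. Vomiting, poor intake or feeling ill could cause that, and could also go with kidney injury; Table 1 itself excludes patients at high risk of dehydration from poor oral intake. If the link between low compliance and AKI differs by arm, those who remain are no longer a randomised comparison, and a benefit can be created or masked.

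**Working it through.** **1. The plan's own figure.** Inputs from Sample size calculations: 25% AKI on placebo; a 60% reduction, so 10% on gemigliptin; one-sided 5%; 80% power; 20% dropout. The unpooled formula gives

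n = (1.645 + 0.842)² × (0.25×0.75 + 0.10×0.90) / 0.15² = 76.3 per group,

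and 76.3 × 1.2 = 91.5. The arcsine formula gives 75.9 × 1.2 = 91.0. So the 91 per group is reproduced, and it includes the dropout allowance.

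**2. The rules side by side.**

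| Participant with under 80% compliance | Consequence in the text |
|---|---|
| Treatments | Removed from the study |
| ITT definition | Included, as randomised |
| PP definition | Out only by not having completed; 80% is not mentioned |
| Sample size | Counted among the 182 analysed |
| Closing creatinine | Not stated whether it is still taken |

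The first row cannot be squared with the second and fourth unless removal is taken to mean something narrower than the words say.

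**3. Removal unrelated to outcome.** This causes no bias, only lost precision. At 25% vs 10%, power with 91 per group is 85.1% one-sided (76.3% two-sided). With 20% removed (0.8 × 91 ≈ 73) it is 77.5% (66.8%).

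**4. Removal related to AKI in one arm.** The documents give no removal rates, so these are assumptions: no drug effect; AKI 25% in both arms; the same share r removed in each arm; on placebo, removal unrelated to AKI; on gemigliptin, removal with probability q without AKI and 3q with AKI. Then

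0.25×3q + 0.75×q = 1.5q = r, so q = r/1.5,

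and AKI among those who remain on gemigliptin is 0.25(1 − 3q)/(1 − r). The remaining number per arm is 91(1 − r), rounded. The last column comes from exact enumeration of both binomial counts with an uncorrected χ² test at two-sided 5%, counting only results that favour gemigliptin.

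| r per arm | Removed with / without AKI, gemigliptin | Apparent AKI, gemigliptin vs placebo | n per arm | Chance of false benefit |
|---|---|---|---|---|
| 3% | 6% / 2% | 24.2% vs 25% | 88 | 3.4% |
| 5% | 10% / 3.3% | 23.7% vs 25% | 86 | 4.0% |
| 10% | 20% / 6.7% | 22.2% vs 25% | 82 | 6.2% |
| 20% | 40% / 13.3% | 18.75% vs 25% | 73 | 14.5% |

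Example for r = 20%: 0.25 × 0.6 / 0.8 = 0.1875. The nominal value is 2.5%. At the one-sided 5% level used for sizing, the 20% case gives about 23% instead of 5%.

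**5. Same link in both arms.** Apparent AKI falls equally in each arm (18.75% in both at r = 20%). The difference stays at zero and the chance of a false benefit stays at about 2.5%.

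**The case against.** The strongest reply is that the sections can be read together. A participant removed for low compliance has not completed the study, so is out of PP, but was randomised, so is in ITT by an unqualified definition. On that reading the 80% rule simply supplies the PP criterion. The outcome may also exist: no interim pill count is described, an 80% threshold on an 8-day course is naturally judged at its end, and the second laboratory visit falls at about the same time. The schedule figure, which might settle the timing, is not available. Handling of missing outcomes may be covered in the full protocol or analysis plan.

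Much of this stands. A reader might infer that removed participants have no closing creatinine and that both the ITT and the PP results become completer analyses. The documents do not show that; loss of the outcome is an inference.

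The mechanism for a difference between arms is also thin. Safety issues lists events to be recorded under either treatment, without saying that they are commoner on gemigliptin. Tablets are identical and blinded, and patients at high risk of dehydration from poor oral intake are excluded. The Table 1 item can be read as poor compliance anticipated at screening, so it is not evidence of a post-randomisation exclusion.

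The reply does not remove the conflict. The text removes people from the study rather than from the PP set, and a later analysis plan cannot recover a sample that was never taken.

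**Conclusion.** The concern holds as a conflict between stated rules that puts primary outcomes at risk. It does not hold as a demonstration that ITT is defeated. As written, the 80% rule can leave randomised participants without the closing creatinine, and the ITT comparison is biased if low compliance is related to AKI differently by arm.

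The size depends on assumptions that the documents do not supply. With a 3:1 link on gemigliptin only, the chance of a false benefit runs from 3.4% at 3% removal to 14.5% at 20%, against 2.5% nominal; with an equal link in both arms there is no inflation. It would be tempting to quote 14.5% as the expected error. That case assigns the whole 20% dropout allowance to compliance removal and makes the link one-sided, neither of which the documents support. It is the top of an assumed range.

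**What to change.** - In Treatments, replace removal from the study with a statement that participants below 80% compliance stay in follow-up, have the already scheduled closing creatinine, and are analysed in ITT in the arm to which they were randomised.
- In Statistical analyses, add the 80% threshold to the PP definition and use it nowhere else.
- In Sample size calculations, make the statement that 182 are analysed consistent with this.
- In Table 1, limit the low-compliance item to what can be judged before randomisation.

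These changes concern data collection and analysis sets only. They add no visit, and recruitment is under way, so an early amendment preserves samples that cannot be recovered later.

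The downside is that the ITT effect may be somewhat diluted. If, as an unfavourable assumption, non-compliant participants on gemigliptin gain nothing, a 10% share gives 0.9 × 10% + 0.1 × 25% = 11.5% AKI against 25%. One-sided power with all 91 per group is then 76.5%, against 81.6% if 10% are lost at random. At a 20% share, AKI is 13% and the powers are 66.4% and 77.4%. That is the price of an estimate protected by randomisation; the PP analysis remains available beside it.

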**Fig. 2 Fig2:**
[figure not shown]
Study schedule. Abbreviations: *R*, randomization; *Wt*, weight; *Ht*, height; *BP*, blood pressure; *CBC*, complete blood count; *AST*, aspartate aminotransferase; *ALT*, alanine aminotransferase; *chol*, cholesterol; *BUN*, blood urea nitrogen; *Cr*, creatinine; *tCO*
_*2*_, total CO_2_; *U*/*A*, urinalysis; *DPP4*, dipeptidyl peptidase 4

### Chemotherapy regimen and precautions

A hydration protocol will be identically applied to both the treatment and control groups. Cisplatin will be mixed with 500 ml of isotonic saline and will be infused into each patient over 30 min. Participants treated with ≥50 mg/m^2^ of cisplatin will receive 2,000 ml of 0.45 % saline and 100 ml of 15 % mannitol. Participants treated with <50 mg/m^2^ of cisplatin will receive 1,000 ml of 0.45 % saline (Table 2).

**Table 2 Tab2:** Hydration protocol

Cisplatin dose	Before and after cisplatin infusion	During cisplatin infusion
≥50 mg/m^2^	2,000 ml of 0.45 % saline with 100 ml of 15 % mannitol	Mix cisplatin in 500 ml of isotonic saline
<50 mg/m^2^	1,000 ml of 0.45 % saline	Mix cisplatin in 500 ml of isotonic saline

### Outcome measures

The primary outcome of interest is the incidence of AKI at 7 days after cisplatin treatment, where AKI is defined as any of the following: an increase in SCr levels of ≥0.3 mg/dl, an increase in SCr levels of 50 % compared with baseline levels, or a decrease in the eGFR by ≥25 % compared with baseline [31–33]. The secondary outcomes will include changes in SCr levels and the eGFR compared with baseline values for 7 days after cisplatin treatment.

### Clinical and laboratory evaluations

The physical examination and medication reviews will be conducted before and after 8 days of treatment. Laboratory evaluations will be performed twice, before and after 8 days of treatment; the laboratory evaluations will include a complete blood count; measurements of the levels of hemoglobin, electrolytes, SCr, calcium, phosphorous, protein, albumin, and glucose; a liver function test; and urinalysis. DPP4 activity and the concentration of the DPP4 inhibitor will be measured in serum and plasma after treatment.

### Safety issues

Any occurrence of headache, diarrhea, upper respiratory tract infection, hypoglycemia, or hypersensitivity reaction will be recorded during treatment with gemigliptin/placebo. All adverse events, including serious adverse events, will be recorded and followed up during the study period or until resolution. All serious adverse events will be graded and reported to investigators and the ethics committee.

### Sample size calculations

No previous study has evaluated the effect of a DPP4 inhibitor on cisplatin-induced AKI. We expect that the incidence of AKI will be 25 % in patients treated with a single dose of cisplatin and that treatment with a DPP4 inhibitor could reduce this incidence by 60 %. We calculated the required sample size for an estimated dropout rate of 20 %, a one-sided level of significance of α = 5 %, and a power of 80 % and found that 91 participants will be needed in each group to find a significant difference using a *χ*^2^ test. A total of 182 participants will be included in the analysis.

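### The stated 91 per group is 4 to 8 short of what the plan's own inputs and 20% dropout require, and the 182 said to be analysed is not reconciled with that dropout

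*Protocol article*

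**What the plan says.** All the inputs stand in one paragraph of the protocol article, under Sample size calculations:

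- Control rate: "We expect that the incidence of AKI will be 25 % in patients treated with a single dose of cisplatin".
- Effect: "treatment with a DPP4 inhibitor could reduce this incidence by 60" %.
- Error rates: "a one-sided level of significance of α = 5 %, and a power of 80" %.
- Dropout: "We calculated the required sample size for an estimated dropout rate of 20" %.
- Result: the authors "found that 91 participants will be needed in each group to find a significant difference".
- Number analysed: "A total of 182 participants will be included in the analysis".

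Statistical analyses names the test: "The incidence of AKI will be compared between the two groups using a *χ*^2^ test". It mentions no continuity correction. The same section puts every randomised participant in the intention-to-treat (ITT) analysis and only those who completed the study in the per-protocol (PP) analysis. Randomization gives 1:1 allocation. The Abstract gives 182 as the number enrolled and randomised.

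**The concern.** The paragraph presents 91 per group as the number that delivers 80% power once a fifth of participants are lost. If 91 does not follow from the inputs beside it, the power claim for the primary outcome is not the one the design supports, and anyone interpreting a null result would start from too favourable a figure.

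The last sentence of the paragraph adds to this. The Abstract uses 182 for the number randomised, and this sentence uses 182 for the number analysed. With 20% dropout expected, one number cannot serve for both the participants randomised and those with an observed outcome.

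**Working it through.** **Inputs.** p1 = 0.25. p2 = 0.25 × (1 − 0.60) = 0.10. Difference d = 0.15, d² = 0.0225. One-sided α = 0.05, z = 1.6449. Power 0.80, z = 0.8416. Dropout 0.20. Allocation 1:1. All come from Sample size calculations, except the allocation (Randomization).

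**Step 1: evaluable participants per group.**

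- *Pooled variance under the null.* The mean rate is 0.175. n = [1.6449 × √(2 × 0.175 × 0.825) + 0.8416 × √(0.25 × 0.75 + 0.10 × 0.90)]² / d² = [1.6449 × √0.28875 + 0.8416 × √0.2775]² / 0.0225 = 78.3, so 79.
- *Unpooled variance.* n = (1.6449 + 0.8416)² × 0.2775 / 0.0225 = 76.25, so 77.
- *Arcsine.* h = 2·asin√0.25 − 2·asin√0.10 = 0.4037. n = 2 × (1.6449 + 0.8416)² / h² = 75.9, so 76.
- *Exact enumeration* of the uncorrected chi-square test over both binomial distributions: power is 79.9% at 75 and 80.4% at 76, so 76.

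**Step 2: allow for 20% dropout.** To keep n after losing a fifth, randomise n / (1 − 0.20).

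| Method | Evaluable n | n / 0.8, rounded up | Total | Shortfall of 91 |
|---|---|---|---|---|
| Pooled | 79 | 99 | 198 | 8 |
| Unpooled | 77 | 97 | 194 | 6 |
| Arcsine | 76 | 95 | 190 | 4 |
| Exact | 76 | 95 | 190 | 4 |

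None of these gives 91.

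**Step 3: can the stated figure be reproduced?** 76 × 1.2 = 91.2, which rounds to 91. This adds 20% of n instead of dividing by 0.8. The document does not show its calculation, so this is a likely source and not a proven one.

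**Step 4: what 91 per group delivers.** 91 × 0.8 = 72.8, about 73 per group. In total, 182 × 0.8 = 145.6, about 146.

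Pooled power at 73 is Φ[(0.15 × √73 − 1.6449 × √0.28875) / √0.2775] = Φ(0.755) = 77.5%. At the same 73 per group the unpooled formula gives 78.5%, the arcsine formula 78.6% and exact enumeration 78.9%. The shortfall from 80% is therefore 1.1 to 2.5 percentage points.

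**Step 5: how much loss can 91 bear?** Power stays at 80% while 76 to 79 per group remain. That is a loss of 1 − 79/91 = 13% (pooled) to 1 − 76/91 = 16% (arcsine or exact), against the 20% planned for.

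**Step 6: the two uses of 182.** If 182 are randomised, about 146 have an outcome after 20% loss. If 182 are to have an outcome, 182 / 0.8 = 227.5, so 228 would have to be randomised.

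**The case against.** **The loss is small and the inputs are soft.** This stands. One to three points of power are less than the uncertainty in the assumptions: the Discussion calls the 60% reduction tentative and moves from an institutional 14.4% to 25% by judgement. It also describes the trial as exploratory phase II and says that more participants cannot be enrolled. All this argues for a modest rating. It does not make 91 the result of the stated calculation.

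**The 182 may simply be the ITT count.** This stands in part. Statistical analyses puts all randomised participants in the ITT set, so the sentence can be read that way, with dropout affecting only the PP set. If all 91 per group had an outcome and the 25% and 10% still applied, power would be 85.0% (pooled) or 85.7% (exact). A reader might therefore infer a flat contradiction, and the text does not go that far. But Clinical and laboratory evaluations schedules blood tests only twice, before and after the 8 days of treatment. A participant lost before the second sample has no post-treatment creatinine, and membership of the ITT set does not supply one. The sentence still needs reconciling with the allowance.

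**Stronger readings that the document does not support.** A reader might infer that 91 is a continuity-corrected size with no dropout allowance, which would put power at 73 per group near 71%. That corrected size is 91.1, which rounds up to 92, and no correction is mentioned anywhere. Nor is its absence from the article a fault. A reader might also cite about 67% power at 73 per group on a two-sided test. The sample size is declared as one-sided, and the Discussion discloses and defends that choice. Sidedness is a separate question and no evidence that 91 fails on its own terms.

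**Conclusion.** The sample size and power are wrong as written, by a small amount. On the plan's own inputs and an uncorrected chi-square test, 95 to 99 per group must be randomised for 80% power after 20% dropout. The stated 91 is 4 to 8 per group short (8 to 16 in total), and about 73 evaluable per group give about 77% to 79% one-sided power.

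This assumes that a dropout has no outcome and that loss is equal in the two groups. The range reflects the choice among standard methods, since the article does not name its formula. The sentence on 182 analysed is an unresolved ambiguity and not a proven contradiction. Severity is modest: the documents do not support calling the trial seriously underpowered on this ground, and neither the design nor the enrolment has to change.

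**What to change.** Keep 182, given the stated limit on enrolment, and restate the end of Sample size calculations along these lines: *182 participants (91 per group) will be randomised; with 20% dropout about 146 (73 per group) will have an outcome, which gives about 77% to 79% one-sided power for 25% versus 10%.*

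Replace the sentence on 182 being analysed with one that fits both the dropout allowance and the sets in Statistical analyses: 182 as the number randomised and so nominally in the ITT set, about 146 as the number expected to have an outcome, and whether the 20% refers to missing outcomes or to exclusion from the PP set.

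The cost is one rewritten paragraph and a slightly less favourable power statement. Recruitment, treatment and the analysis method are untouched.
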